## Abstract

**Background:**

Atopic dermatitis (AD) is a common inflammatory skin disease associated with substantial disease burden. Traditional Chinese medicine (TCM) has shown beneficial effects in improving AD symptoms and reducing recurrence. Inflammation Formula Number 1 (IFN-1), a TCM prescription consisting of 10 herbal ingredients, has demonstrated favorable efficacy in clinical practice. However, traditional decoction preparation is time-consuming and inconvenient for long-term standardized use. Granule formulations may improve convenience, stability, and quality control, but their dose-response relationship and equivalence to traditional decoction remain unclear.

**Objective:**

This multicenter, prospective, randomized equivalence trial aims to evaluate the efficacy, safety, and dose-response relationship of IFN-1 granule formulations compared with traditional decoction in patients with mild to moderate AD.

**Methods:**

A total of 300 patients with mild to moderate AD aged 18 to 60 years will be recruited from 5 hospitals between April 2026 and January 2027. Participants will be randomly assigned in a 2:2:1:1 ratio to the traditional decoction group (n=100, 33.3%), standard-dose granule group (n=100, 33.3%), two-thirds dose granule group (n=50, 16.7%), or one-tenth dose granule group (n=50, 16.7%). All groups will receive 4 weeks of treatment. The primary end point is the proportion of patients achieving at least 50% improvement in the Eczema Area and Severity Index (EASI) at week 4. Secondary outcomes include EASI75, EASI90, Investigator Global Assessment score of 0 or 1, body surface area involvement, Dermatology Life Quality Index, pruritus numerical rating scale, Patient-Oriented Eczema Measure, and TCM syndrome scores. Outcomes will be assessed at baseline and weeks 1, 2, and 4. Statistical analyses will be conducted using SAS (version 9.4). Equivalence will be evaluated using a 2-sided 95% CI approach with a predefined equivalence margin of −15% to +15%.

**Results:**

Funding for this study was obtained in 2025. Ethical approval was granted by the Ethics Committee of Shanghai Skin Disease Hospital in December 2025, and the trial was registered with the International Traditional Medicine Clinical Trial Registry (ITMCTR2026000452). Participant recruitment is scheduled to begin in April 2026 and continue through January 2027. No patients were recruited at the time of manuscript submission. Data analysis is expected to commence in March 2027, and the primary study findings are anticipated to be published in 2028.

**Conclusions:**

This trial will determine whether IFN-1 granules achieve efficacy comparable to traditional decoction while improving treatment convenience. The findings may provide evidence for dose optimization and standardized clinical application of TCM granule formulations in AD management.

## Introduction

### Background

Atopic dermatitis (AD) is a common inflammatory skin disorder, characterized by eczematous lesions accompanied by persistent and severe pruritus [1]. Epidemiological studies indicated that more than 100 million adults and 100 million children worldwide are affected by AD [2], and its incidence has increased markedly over the past decade both globally and in China [3,4]. Owing to its severe pruritus, AD significantly impairs patients’ quality of life [5]. Consequently, AD is considered one of the nonfatal skin disorders associated with the highest disease burden [6].

Currently, the treatment of mild to moderate AD is still primarily focused on topical therapy, which constitutes the foundation of treatment for AD [7]. The commonly used topical treatments include corticosteroids and calcineurin inhibitors, which can effectively suppress local inflammatory responses and relieve skin lesions and pruritus [8]. However, the potential adverse effects of these treatments limit their long-term clinical use [9,10]. Meanwhile, there is still a lack of safe, effective oral treatment options for patients with mild to moderate AD. Therefore, the development of a safe and effective oral therapy for AD treatment could fill a gap in the current treatment landscape for mild to moderate AD.

Traditional Chinese medicine (TCM) offers a feasible solution to the current lack of oral therapies for mild to moderate AD, with demonstrated advantages including safety, efficacy, and a low recurrence rate. On the basis of the TCM principle of “cooling the blood and calming yang,” Inflammation Formula Number 1 (IFN-1) was developed and consists of 10 herbs: *Rehmannia glutinosa* (Sheng Di Huang), *Salvia miltiorrhiza* (Dan Shen), *Saposhnikovia divaricata* (Fang Feng), *Isatis indigotica* (Da Qing Ye), *Angelica sinensis* (Dang Gui), *Sophora flavescens* (Ku Shen), *Scutellaria baicalensis* (Huang Qin), *Prunella vulgaris* (Xia Ku Cao), *Dictamnus dasycarpus* (Bai Xian Pi), and *Glycyrrhiza uralensis* (Gan Cao). The clinical efficacy of IFN-1 in treating AD has been well established, with a favorable safety profile. However, the traditional decoction form, while effective, poses challenges for standardized clinical use due to the time-consuming preparation process. Granule formulations offer advantages in convenience, stability, and quality control.

With the increased clinical use of IFN-1 in granule form, a lack of evidence-based guidance regarding dose conversion and therapeutic equivalence between granules and traditional decoctions has become a key barrier to wider application. On the basis of multicenter intervention data, this study will construct a dosage form dose-response model to define the minimum effective dose and the recommended dose range for granule administration, and to explore stratified application strategies across different health care settings. The results are expected to provide a scientific basis for the standardized use of Chinese herbal granules and the modernization of TCM practice.

### Objectives

This study evaluates the clinical outcomes under standard and reduced dosages of IFN-1 to construct a dosage form dose-response equivalence model and to clarify the efficacy and safety profiles of its traditional decoction and granules. Ultimately, this study aims to establish a scientific framework for the dose-response relationship of TCM compound granules and formulate standardized clinical application guidelines, providing critical data support for the standardized use of TCM.

## Methods

### Study Design

This study is a multicenter, prospective, randomized clinical trial designed to evaluate the clinical efficacy, safety, and dose-response relationship of IFN-1 administered at a standard dose and reduced doses (granule two-thirds dose and granule one-tenth dose). The study protocol was developed in accordance with the SPIRIT (Standard Protocol Items: Recommendations for Interventional Trials) statement [11]. This study will be conducted according to protocol version 1 (date 2025-10-30). From April 2026 to January 2027, patients with mild to moderate AD will be consecutively recruited from 5 centers, including Shanghai Skin Disease Hospital, Yueyang Hospital of Integrated Traditional Chinese and Western Medicine affiliated with Shanghai University of Traditional Chinese Medicine, Bengbu Third Hospital, Guangzhou Dermatology Hospital, and the Affiliated Hospital of Gansu University of Chinese Medicine. A total of 300 eligible patients with mild to moderate AD will be randomly allocated in a 2:2:1:1 ratio to the traditional decoction group (n=100, 33.3%), standard-dose granule group (n=100, 33.3%), two-thirds dose granule group (n=50, 16.7%), and one-tenth dose granule group (n=50, 16.7%). Patients in all 4 groups will receive treatment for a duration of 4 weeks, during which treatment response and disease progression will be systematically assessed and recorded. The study flow is illustrated in Figure 1.

**Figure 1. F1:**
[figure not shown]
Clinical trial flowchart. AD: atopic dermatitis; BSA: body surface area; DLQI: Dermatology Life Quality Index; EASI: Eczema Area and Severity Index; IGA: Investigator Global Assessment; PNRS: Pruritus Numeric Rating Scale; POEM: Patient-Oriented Eczema Measure; TCM: traditional Chinese medicine.

### Inclusion Criteria

The inclusion criteria for patients with mild to moderate AD are as follows: (1) aged 18 to 60 years, regardless of sex; (2) a clinical diagnosis meeting the Williams diagnostic criteria for AD, with an Eczema Area and Severity Index (EASI) score ≤21 and body surface area (BSA) involvement between 3% and 20%; (3) meeting the TCM diagnostic criteria for wind-damp-heat stagnation syndrome (red, swollen skin with severe burning pruritus, oozing and yellow crusting due to scratching, often accompanied by dry mouth, dark urine, a red tongue with yellow greasy coating, and a slippery-rapid or wiry-rapid pulse; the condition recurs and worsens in hot, humid environments); (4) Investigator Global Assessment (IGA) score ≥3; and (5) provision of written informed consent [12].

### Exclusion Criteria

The exclusion criteria for this study are as follows: (1) pregnant or lactating women; (2) receipt of systemic treatment for AD (including immunosuppressants or biologic agents) within the past 1 month or topical therapy or phototherapy within the past 2 weeks; (3) known allergy or hypersensitivity to any component of the 10 herbs in IFN-1; (4) presence of severe systemic diseases involving the cardiovascular, pulmonary, gastrointestinal, hepatic, or renal systems, or severe psychiatric disorders; (5) presence of systemic diseases or active skin diseases that may interfere with the evaluation of study outcomes, or skin conditions at the target lesion site such as scars or tattoos; (6) participation in another clinical trial within the past 1 month; (7) communication barriers or poor treatment adherence, or inability to independently complete the questionnaires; and (8) any other condition that, in the investigator’s judgment, may pose significant risk to the patient or confound the study results and therefore warrants exclusion.

### Sample Size

This study is designed as an equivalence clinical trial to compare the traditional decoction and the standard-dose granule of IFN-1, with the primary outcome being the proportion of patients with mild to moderate AD achieving EASI50 after 4 weeks of treatment. EASI50 is defined as the percentage of patients achieving ≥50% improvement in EASI score from baseline, reflecting the treatment’s effectiveness in skin lesion improvement. On the basis of previous studies, the EASI50 rate is expected to be 90% in both the traditional decoction group and the granule group at the standard dose. Setting the equivalence margin at Δ=15%, α=.05 (2-sided), and β=.20, the required sample sizes under a 2:1 allocation are 94 and 47, respectively. Considering a 5% dropout rate, the sample sizes are increased to 100 and 50 for the decoction group and the granule standard-dose group, respectively. To explore the dose-response relationship, we include a two-thirds dose granule group (n=50) and a one-tenth dose granule group (n=50). Additionally, 50 patients are added to the standard-dose granule group to strengthen the robustness of the findings. The final study therefore uses a 4-arm parallel design with an allocation ratio of 2:2:1:1 into traditional decoction (n=100), standard-dose granule (n=100), two-thirds dose granule (n=50), and one-tenth dose granule (n=50).

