### Statistical Analysis

Statistical analyses will be performed using SAS (version 9.4). The primary analysis will follow the per-protocol principle, with supportive analyses conducted under the intention-to-treat framework including all randomized patients. Missing data will be handled under the missing-at-random assumption using sequential regression multiple imputation. This study is designed as an equivalence trial, with the primary end point being the proportion of patients achieving EASI50 at week 4. The prespecified equivalence margin (Δ) was set at 15% based on clinical considerations. Equivalence will be assessed using the 2-sided 95% CI approach: the difference in EASI50 response rates between groups will be estimated, and the corresponding 95% CI will be constructed using the chi-square test. Equivalence will be concluded if and only if the entire CI lies within the predefined margin of −15% to +15%. For intergroup comparisons among the 4 treatment groups, an overall test will first be performed. Subsequently, pairwise comparisons will be conducted where appropriate. Between-group comparisons will be performed using the Student *t* test (2-tailed) or Wilcoxon rank-sum test, as appropriate. For multiple pairwise comparisons, Bonferroni correction will be applied to control for type I error. Linear mixed-effects models will be applied for continuous outcomes, and generalized linear mixed models will be used for binary outcomes, with subject-specific random effects to account for within-subject correlation and to appropriately handle missing data. Categorical variables will be expressed as frequencies and percentages and compared using the chi-square test or Fisher exact test. In addition, a dose-response model will be constructed to characterize the dose-response relationship of granules and to explore the formulation conversion between granules and traditional decoction. Except for the equivalence testing described above, a 2-sided *P*<.05 will be considered statistically significant.

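### The stated requirement of 94 and 47 patients comes from a one-bound non-inferiority formula, not the equivalence rule; the planned 100 versus 100 comparison is still adequately powered

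*Protocol article*

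**What the plan says.** The Sample Size section of the protocol article sets the purpose: "This study is designed as an equivalence clinical trial to compare the traditional decoction and the standard-dose granule of IFN-1". Its planning assumptions are that "the EASI50 rate is expected to be 90% in both the traditional decoction group and the granule group at the standard dose", and "Setting the equivalence margin at Δ=15%, α=.05 (2-sided), and β=.20". From these it concludes that "the required sample sizes under a 2:1 allocation are 94 and 47, respectively". It then allows for losses: "Considering a 5% dropout rate, the sample sizes are increased to 100 and 50" for decoction and standard-dose granule. Last, it enlarges the granule arm: "Additionally, 50 patients are added to the standard-dose granule group to strengthen the robustness of the findings". The comparison to be run is therefore 100 versus 100, as the Abstract, Study Design and Randomization sections also state.

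The Statistical Analysis section fixes the decision rule. A two-sided 95% CI is built for the difference in EASI50 rates, and "Equivalence will be concluded if and only if the entire CI lies within the predefined margin" of −15% to +15%.

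**The concern.** An equivalence claim can fail on either side: the lower limit can fall below −15 points or the upper limit can rise above +15 points. When the true difference is zero, as assumed here, the two failures are equally likely, so each may use only half of beta. A calculation that gives the whole of beta to one side answers a non-inferiority question and returns too small a number. The figures 94 and 47 look like such a calculation.

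What is at stake is the justification for the size of the primary comparison. As written, a reader learns that 100 and 50 patients suffice and that the next 50 are a bonus. If recruitment lagged, those 50 would look expendable, although without them the stated power is not reached.

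**Working it through.** **Inputs.** All come from the Sample Size section: p = 0.90 in both arms, so p(1−p) = 0.09; margin 0.15, with square 0.0225; two-sided alpha .05, so each bound is tested at .025 with z = 1.960; beta = .20; allocation 2:1; dropout 5%. The rule that the whole 95% CI must lie inside the margin comes from the Statistical Analysis section.

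**1. Reproducing the plan's figure.** For 2:1 allocation, the smaller arm is n = (z_α + z_β)² × 0.09 × 1.5 / 0.0225 = 6 × (z_α + z_β)².
- One bound, z_β = z(.80) = 0.842: 6 × (1.960 + 0.842)² = 47.09, and twice that is 94.19. This matches the stated 47 and 94, apart from rounding down.
- Other readings give a different larger arm: one-bound at one-sided .05 gives 75; two-bound with a 90% CI gives 102.8 (smaller arm 51.4); superiority of 90% over 75% gives 142 to 162, depending on the variant. None of them reproduces 94.

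**2. The equivalence requirement.** With a true difference of zero, beta is split, so z(.80) is replaced by z(.90) = 1.282.
- 2:1: 6 × (1.960 + 1.282)² = 63.04 and 126.09, that is 64 and 127 evaluable. After 5% dropout: 64/0.95 and 127/0.95, that is 68 and 134.
- 1:1: n per arm = 0.09 × 2 / 0.0225 × (1.960 + 1.282)² = 84.06, that is 85 evaluable. After 5% dropout: 85/0.95, that is 90.

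**3. Power under the trial's own rule.** SE = √[0.09 × (1/n₁ + 1/n₂)]. One-bound power is Φ(0.15/SE − 1.96); two-bound power is 2Φ(0.15/SE − 1.96) − 1.

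| Decoction / standard granule | One bound | Both bounds (approx.) | Exact, Wald | Exact, pooled SE | Exact, Newcombe |
|---|---|---|---|---|---|
| 94 / 47 | 79.9% | 59.8% | 62.6% | 61.6% | 52.8% |
| 100 / 50 | 82.3% | 64.6% | 65.2% | 65.0% | 58.2% |
| 95 / 95 | 93.1% | 86.3% | 86.6% | 84.8% | 82.6% |
| 100 / 100 | 94.2% | 88.5% | 88.0% | 87.0% | 84.7% |

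The exact columns enumerate all pairs of binomial outcomes at a 90% rate in both arms. As an example, at 94/47 SE = √[0.09 × (1/94 + 1/47)] = 0.0536, 0.15/0.0536 − 1.96 = 0.84, Φ = 0.799, and 2 × 0.799 − 1 = 0.598. The 79.9% in the first row is the stated beta of .20; it holds for one bound only.

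**4. What the added 50 do.** Going from 100/50 to 100/100 raises power from 64.6% to 88.5% with no losses. With 5% dropout, 100/100 becomes 95/95 and gives 86.3%. In a balanced design the requirement is 90 randomised per arm. Measured against that, 90 − 50 = 40 of the 50 added granule patients belong to the requirement and 10 are spare.

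**The case against.** The strongest reply is that 94 and 47 are an intermediate step and no one will analyse a 94/47 comparison. The design that will be run has 100 in each of the two arms. It exceeds the correct 1:1 requirement of 85 evaluable and passes 80% power under each interval method in the table. No allocation, analysis or decision rule has to change. All of this stands, and it limits the consequence to the justification. It does not make the sentence right: the article states a required size for an equivalence trial with beta .20, and that size does not deliver beta .20 under the article's own rule.

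A second reply is that a condensed article need not restate power for the final arms. That also stands, and the missing restatement is not the finding. The finding is a figure that is stated and wrong.

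A reader might go further and infer that the two 50-patient reduced-dose arms are underpowered for equivalence. The document does not support this. The Sample Size section confines the equivalence design to decoction against standard-dose granule, adds the smaller arms to explore dose-response, and gives neither a power target nor an expected response rate for them. The Statistical Analysis section does not repeat which pair is meant, but read with the Sample Size section the pair is clear.

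**Conclusion.** Wrong as written. The 94 and 47 are a one-bound non-inferiority size presented as an equivalence size. Under the rule that the whole 95% CI must lie within ±15 points they give about 60% power rather than 80% (53% to 63% by exact enumeration, depending on the interval). The inflated 100 and 50 give about 65% even with no losses.

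A reader might conclude that the trial is underpowered. It is not, on its stated assumptions: with a 90% rate in both arms, no true difference and 5% dropout, 95 versus 95 gives about 86% by normal approximation and about 83% to 87% by exact Newcombe and Wald enumeration. The consequence is a wrong sample-size justification, which hides that the enlarged granule arm is what takes the comparison past 80%.

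These powers rest on the 90% assumption. A reader might also argue that a lower rate would leave the trial short, but the document attributes the 90% to previous studies and contains nothing that shows it to be wrong, so no finding is made on it.

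**What to change.** In the Sample Size section, replace the 2:1 calculation with the two one-sided tests calculation for the 1:1 comparison that will be analysed. It should say that:
- with 90% in both arms, a 15-point margin, a two-sided 95% CI and 80% power, about 85 evaluable patients per arm are required (normal approximation), or about 90 after 5% dropout, and 100 per arm are planned;
- the resulting power at 95 evaluable per arm is about 86% by normal approximation, or the exact value for the interval method to be used;
- the enlargement of the standard-dose granule arm from 50 to 100 is needed to reach the stated power, in place of the present description of it as added robustness.

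The cost is rewording one paragraph. No patients are added, and the allocation, margin and decision rule stay as they are.

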### Randomization

This study is planned to use a stratified block randomization method with “study hospital” as the stratification factor. A total of 300 patients with mild to moderate AD will be randomly assigned in a 2:2:1:1 ratio to the traditional decoction group (n=100, 33.3%), standard-dose granule group (n=100, 33.3%), two-thirds dose granule group (n=50, 16.7%), and one-tenth dose granule group (n=50, 16.7%). The randomization scheme and implementation will be monitored by dedicated statisticians at the Clinical Research Center of Shanghai Skin Disease Hospital. Randomization codes will be generated by the same center and concealed in opaque, sealed envelopes. After recruitment screening, the envelope will be opened by study personnel, and the patient will receive the treatment corresponding to the assigned random number.

### Blinding

This study is designed as an open-label trial, in which both the participants and the investigators will be aware of the treatment assignments. However, the outcome assessors and the statisticians will be blinded throughout the trial period to prevent potential information bias.

### Interventions

In this study, patients in the traditional decoction group, the standard-dose granule group, the two-thirds dose granule group, and the one-tenth dose granule group will receive treatment twice daily, 30 minutes after breakfast and dinner, at a dose of 200 mL for 4 consecutive weeks. All patients will receive baseline therapy with desonide cream combined with urea ointment, applied twice daily for 14 days. After 14 days, desonide cream will be discontinued, and urea ointment will be continued alone for an additional 14 days. The detailed composition of IFN-1 is presented in Table 1, and the dosage of each herbal component in different formulations is shown in Table 2. The IFN-1 granules used in this study were manufactured by Guangdong Efang Pharmaceutical Co, Ltd in compliance with Good Manufacturing Practice. Quality control procedures included authentication of raw herbal materials, testing for heavy metals, pesticide residues, microbial contamination, and batch-to-batch consistency, following the standards of the Chinese Pharmacopoeia (2020 edition).

**Table 1. T1:** Detailed drug composition of Inflammation Formula Number 1 (IFN-1).

Chinese name	Latin name	Pharmacologic activity
Sheng Di Huang	*Rehmannia glutinosa*	Immunomodulation and anti-inflammatory
Dan Shen	*Salvia miltiorrhiza*	Microcirculation improvement and antioxidant
Fang Feng	*Saposhnikovia divaricata*	Antiallergic and analgesic
Da Qing Ye	*Isatis indigotica*	Anti-inflammatory and antiviral
Dang Gui	*Angelica sinensis*	Immunomodulatory and antithrombotic
Ku Shen	*Sophora flavescens*	Antipruritic and anti-inflammatory
Huang Qin	*Scutellaria baicalensis*	Antiallergic, antibacterial, and antifungal
Xia Ku Cao	*Prunella vulgaris*	Antioxidant and immunosuppressive
Bai Xian Pi	*Dictamnus dasycarpus*	Anti-inflammatory and antifungal
Gan Cao	*Glycyrrhiza uralensis*	Steroid-like activity and anti-inflammatory

**Table 2. T2:** Composition and dosage of Inflammation Formula Number 1 in different formulations.

Chinese name	Traditional decoction (g)	Standard-dose granule (g)	Two-thirds dose granule (g)	One-tenth dose granule (g)
Sheng Di Huang	15	15	10	1.5
Dan Shen	9	9	6	0.9
Fang Feng	6	6	4	0.6
Da Qing Ye	9	9	6	0.9
Dang Gui	9	9	6	0.9
Ku Shen	9	9	6	0.9
Huang Qin	9	9	6	0.9
Xia Ku Cao	9	9	6	0.9
Bai Xian Pi	9	9	6	0.9
Gan Cao	6	6	4	0.6

